### Statistical Analysis

#### Sample Size Estimation

A sample size of 80 subjects, 40 per arm, is sufficient to detect a difference of 1.5 between the two groups (control vs intervention) in pain intensity scores, assuming equal standard deviation of 2.5, using a two-tailed *t* test of difference between means, with 80% power, and a 2-sided alpha of .05. Patients in the experimental group who decide to never use the device during hospitalization will be excluded from the study.

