#### Randomization and Blinding

An independent researcher with no direct contact with the participants will use a computer-generated randomization with a 1:1 ratio and permutated blocks to optimize balance in each treatment arm. Due to the nature of the study, participants, care providers, and researchers cannot be blinded for the allocated treatment. However, the data analysis will be blind, as all of the patients receive a unique study code, under which their data is stored in the database.

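### The stated 80% power does not follow from its own inputs: 40 per arm gives about 75% for the t test named, and that test would need 45 per arm

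*Protocol article*

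**What the plan says.** The Sample Size Estimation section of the protocol article gives the whole calculation in one sentence. It says that "A sample size of 80 subjects, 40 per arm, is sufficient to detect a difference of 1.5 between the two groups" in pain intensity scores, "assuming equal standard deviation of 2.5, using a two-tailed" *t* test for a difference between means, "with 80% power, and a 2-sided alpha of .05". The Randomization and Blinding section adds equal allocation: "computer-generated randomization with a 1:1 ratio and permutated blocks".

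The sizing sentence mentions no allowance for dropout, no within-patient correlation and no other adjustment. The sentence after it removes from the study any experimental-arm patient who never uses the device. The Statistical Analysis section then plans a different method for the primary outcome, a mixed model analysis of variance on the repeated pain scores.

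**The concern.** Sample size, difference, SD, test, alpha and power are all stated, so any one of them can be checked against the rest. A standardised difference of 0.60 at 80% power and two-sided 5% alpha usually calls for about 44 or 45 per arm, so 40 looked too few.

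This sentence is the only quantitative justification of the trial's size, and it concerns the primary outcome. If the power is overstated, a null result will be read as coming from a better-powered comparison than the inputs support. On the stated t test, the chance of missing a true 1.5-point difference would be about one in four instead of one in five.

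**Working it through.** **Inputs**, all from Sample Size Estimation except the allocation ratio, which is from Randomization and Blinding: n = 40 per arm, difference δ = 1.5, common SD σ = 2.5, two-sample *t* test, two-sided α = .05, target power 80%, ratio 1:1.

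**Standardised difference.** d = δ/σ = 1.5/2.5 = 0.60.

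**Attempt to reproduce the stated power at 40 per arm.**
- Noncentrality: d·√(n/2) = 0.60 × √20 = 2.683.
- *t* test: 2 × 40 − 2 = 78 degrees of freedom, critical value 1.991. The noncentral *t* distribution gives power **75.5%**.
- Normal approximation: Φ(2.683 − 1.960) = Φ(0.723) = **76.5%**.

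Neither gives 80%.

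**Sample size for 80% power.**
- Normal approximation: n = 2(1.960 + 0.842)²/0.60² = 43.6, so 44 per arm (88 in total).
- *t* test: the solution is 44.6, so **45 per arm (90 in total)**. Power is 79.5% at 44 per arm and 80.4% at 45.

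The shortfall against the *t* test is 90 − 80 = 10 patients, or 10/90 = 11% of the number required.

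**What 40 per arm does support at 80% power (*t* test).** The detectable standardised difference is 0.634.
- With SD 2.5, the detectable difference is 0.634 × 2.5 = **1.59 points**.
- With a difference of 1.5, the SD must be no more than 1.5/0.634 = **2.36**.

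**Could another reading explain the figure?** A one-sided test at .05 gives 84.5% power at 40 per arm (85.0% by the normal approximation) and needs only 35 to 36 per arm. It does not reproduce 40 per arm at 80%, and the text says two-sided. A dropout allowance would make the planned number larger than the bare calculation, whereas here it is smaller.

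**Effect of exclusions (illustration only).** The article gives no expected number of never-users. If 4 experimental patients were excluded and not replaced (36 v 40), *t* test power would be 73%. If 8 were excluded (32 v 40), it would be 70%.

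**The case against.** The strongest reply is that the *t* test is not the planned primary analysis. Pain is measured repeatedly and analysed by a mixed model, which averages over assessments and can be more powerful. This can be sized if 2.5 is taken as the SD of a single assessment and all pairs of assessments are assumed equally correlated with correlation ρ. The SD of a patient's mean over m assessments is then 2.5 × √[(1 + (m − 1)ρ)/m]. Twelve-hourly scores (Primary Outcome) over a 5-day stay (Recruitment Procedure) give m = 10. With 40 per arm:

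| Assumed ρ | SD of mean | Power for 1.5 points |
|---|---|---|
| 0.5 | 1.85 | 95% |
| 0.7 | 2.14 | 87% |
| 0.8 | 2.26 | 83% |
| 0.9 | 2.38 | 79% |

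With 5 assessments the corresponding powers are 93%, 86%, 82% and 79%. The real analysis could therefore well exceed 80% power. For that reason the 24.5% risk of missing the effect (100% − 75.5%) belongs to the *t* test in the sizing sentence and not necessarily to the trial.

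This part of the objection stands, but it does not rescue the sentence. The article attributes its 80% to a *t* test, gives no correlation, and does not say whether 2.5 refers to one score or to a patient's mean. If it is already the SD of the mean, the gain disappears.

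It is also fair to say that the gap is modest, that it biases no estimate and inflates no type I error, and that the never-user figures rest on assumed counts. The main point does not depend on those counts.

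**Conclusion.** The concern holds. On the article's own inputs, 40 per arm gives 75.5% power and not 80%, a shortfall of about 4.5 percentage points, and the stated *t* test would need 45 per arm. This rests on nothing outside the article: only the stated difference, SD, test, alpha and equal allocation, with all 80 patients contributing. The power of the planned mixed model cannot be determined from the article. It ranges from about 79% to 95% over assumed correlations of 0.9 to 0.5 with 10 assessments. The error is moderate in size, but it sits in the trial's key design figure and should be corrected.

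**What to change.** Correct the sizing sentence in one of two ways.

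1. **Keep the *t* test and state its true power.** Suggested wording: 80 patients (40 per arm) give about 75% power to detect a difference of 1.5 points, or 80% power for about 1.6 points, assuming an SD of 2.5, a two-sided alpha of .05 and a two-sample *t* test.
2. **Keep an 80% claim at 80 patients by sizing the planned analysis.** State that the target is the group difference in the mean of the repeated scores. Give the number of assessments and the assumed within-patient correlation with its source, and say that 2.5 is the SD of a single score. For example, 10 assessments with a correlation of 0.8 give about 83%.

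In either case, say whether 80 is the number randomised or the number analysed, since the next sentence allows exclusions from one arm.

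The cost is a change of wording. Under the first option the stated power becomes slightly less favourable. Neither option needs extra patients or a change in procedures.

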Our goal is to help patients with lung cancer post-operative acute pain gain better control of their symptoms using this innovative, neurofeedback-based pain-control strategy. We hypothesize that patients randomized to receive the intervention will have better pain outcomes, measured by pain intensity, and better medical and psychological outcomes compared with patients receiving usual care.

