### Recruitment Procedure

All patients who are planned to undergo a thoracotomy for lung resection at the European Institute of Oncology, thoracic surgery unit, are considered potential candidates for the present study. Once admitted in the hospital, they will be screened by a trained research assistant to verify their eligibility. Eligible patients will be asked to sign the informed consent, and then randomly assigned to the intervention or control groups. All participants will be instructed to continue to receive medical care from physicians as usual. Subjects included in the intervention arm will be trained on the use of the technology and relaxation technique prior to the operation by a research assistant. They will also receive a MindSet device and tablet with the app Focus Pocus installed on it, for the entire duration of hospitalization (5 days).

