#### Intervention Group (Neurofeedback and Usual Care)

Patients included in the intervention arm will continue to receive the standard care consisting of intercostal analgesia and intravenous pain killers. In addition to it, they will be encouraged to use the MindWave device to manage their pain on-demand and every time they think they need it. During the hospitalization period, patients assigned to the intervention group will also be asked to evaluate their pain over the past 12 hours on a daily basis until their discharge from hospital.

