#### Control Group

Subjects assigned to the control arm will receive only the standard care. In adjunct, they will also be asked to evaluate their pain over the past 12 hours, every day starting from the operation until their discharge from hospital.

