#### Primary Outcome

The primary outcome measurement is pain intensity, measured as a continuous outcome. It will be assessed quantitatively with the Numeric Pain Rating Scale (NRS) [47]. The paper version of the questionnaire will be self-administered. Participants will be asked to complete it starting from 12 hours after the operation, and every 12 hours during the entire hospitalization period.

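### Intervention patients who never use the device are dropped after randomisation, with no counterpart in the control arm, so the analysed groups are no longer the randomised groups

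*Protocol article*

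**What the plan says.** - **Exclusion rule** (Protocol article, Sample Size Estimation): "Patients in the experimental group who decide to never use the device during hospitalization will be excluded from the study".
- **Timing** (Recruitment Procedure): "Eligible patients will be asked to sign the informed consent, and then randomly assigned to the intervention or control groups". Intervention patients "will be trained on the use of the technology and relaxation technique prior to the operation by a research assistant". Whether a patient uses the device during the stay is therefore known only after allocation.
- **What drives use** (Intervention Group): "they will be encouraged to use the MindWave device to manage their pain on-demand and every time they think they need it".
- **Control arm** (Control Group): "Subjects assigned to the control arm will receive only the standard care".
- **Outcome** (Primary Outcome): "The primary outcome measurement is pain intensity, measured as a continuous outcome", scored on the NRS every 12 hours throughout the hospital stay.
- **Blinding** (Randomization and Blinding): "participants, care providers, and researchers cannot be blinded for the allocated treatment".
- **Hypothesis** (end of the Background): "We hypothesize that patients randomized to receive the intervention will have better pain outcomes".
- **Primary analysis** (Statistical Analysis): a mixed-model analysis of variance with assigned treatment as the between-group factor. Patients already excluded from the study cannot enter that model, and no statement elsewhere in the article brings them back.

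**The concern.** Randomisation makes the two arms comparable at allocation. This rule then removes patients from one arm according to what they do afterwards. Because use depends on felt need, that behaviour is plausibly tied to pain, sedation, complications or distress. Patients of the same kind in the control arm have no device to ignore, so they remain.

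The direction cannot be told in advance. If never-users are too ill or too sore to play, dropping them lowers mean pain in the intervention arm and flatters the device. If they have too little pain to bother, dropping them works against it.

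The rule also changes the question. The hypothesis concerns patients randomised to the intervention, but the analysed patients would be those who chose to use it. Exclusion from the study, read literally, also reaches opioid use, anxiety, blood tests, chest x-ray and the 1- and 4-month assessments. It takes every zero out of the engagement outcome, so engagement would be overstated. Finally, the wording refers to a decision never to use the device and does not say how a patient too unwell to use it is classed. In an open-label trial that judgement is made with the allocation known.

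**Working it through.** **Inputs from the protocol (Sample Size Estimation):** 40 per arm, target difference 1.5, SD 2.5 in both arms, two-sided alpha 0.05, 80% power, *t* test.

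**Inputs assumed, because the documents give none:** *f*, the share of patients who never use the device (5% to 30%), and *d*, the difference in mean NRS between never-users and users (1 to 2.5 points). The *t* test on one score per patient stands in for the planned mixed model.

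**Step 1. The plan's own figure.** The standardised difference is 1.5/2.5 = 0.6. The normal approximation gives n = 2 × (1.96 + 0.842)² / 0.6² = 43.6, so 44 per arm; the *t* test needs 45. At 40 per arm, *t*-test power is 75.5%, not 80%. That shortfall is a separate matter, but 75.5% is the right baseline for the power figures below.

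**Step 2. Bias with no true effect.** Let users have mean μ and never-users μ + d. The control mean is μ + f·d, since all its patients stay in. The intervention mean after exclusion is μ. The size of the bias is therefore f × d.

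**Step 3. Type I error.** Holding the overall SD at 2.5, the variance among users is 6.25 − f(1−f)d². The standard error is SE = √[variance among users / (40(1−f)) + 6.25/40]. The rejection probability comes from the noncentral *t* with noncentrality f·d/SE.

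For f = 20%, d = 2: variance among users = 6.25 − 0.16 × 4 = 5.61; SE = √(5.61/32 + 6.25/40) = 0.576; noncentrality = 0.40/0.576 = 0.69.

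| f | d | Bias (points) | Share of 1.5 | Type I error, formula | Type I error, simulated (20,000 runs) |
|---|---|---|---|---|---|
| 5% | 1 | 0.05 | 3% | 5.1% | 5.1% |
| 5% | 2 | 0.10 | 7% | 5.4% | 5.3% |
| 10% | 1 | 0.10 | 7% | 5.3% | 5.3% |
| 10% | 2 | 0.20 | 13% | 6.4% | 6.3% |
| 20% | 1 | 0.20 | 13% | 6.3% | 6.4% |
| 20% | 2 | 0.40 | 27% | 10.5% | 10.0% |
| 30% | 2 | 0.60 | 40% | 17.0% | 15.9% |
| 30% | 2.5 | 0.75 | 50% | 24.9% | 23.5% |

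The simulation used the pooled-variance *t* test and let the number of never-users vary. It runs slightly below the formula at the upper end.

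**Step 4. Power, for a true 1.5-point effect.** The second column drops never-users without replacing them and takes d = 0, so there is no bias. The remaining columns keep everyone and assume no device effect in never-users, so the effect becomes 1.5 × (1 − f).

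| f | Power, never-users dropped | Diluted effect, all kept | Power at 40 per arm, all kept | n per arm for 80%, all kept |
|---|---|---|---|---|
| 5% | 74.4% | 1.425 | 71.1% | 50 |
| 10% | 73.2% | 1.35 | 66.5% | 55 |
| 20% | 70.4% | 1.20 | 56.4% | 70 |
| 30% | 67.0% | 1.05 | 45.8% | 90 |

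**The case against.** The best reply is that the damage may be small. A single use keeps a patient in. Patients have consented, been trained for 45 to 60 minutes until they can work the device alone, and have it at the bedside. A never-user share of 5% or less is quite possible, and then the error rate hardly moves. A gap of 2 points is 0.8 SD, which is large for a difference in means, and if both the very sore and the nearly pain-free abstain, the net gap shrinks. This stands: the 10% to 25% error rates belong to the adverse end of the assumed range.

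Three further points also stand.

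- The calculation is not the planned analysis. A constant offset between never-users and users would bias a group main effect but not a group-by-time term, and the protocol does not say which is decisive. Averaging repeated scores would also change the SD.
- The fall to 70% power at 20% non-use is measured from 75.5%, so the exclusion costs about 5 points. The rest of the gap to 80% comes from the sample-size calculation.
- Clinical and radiological follow-up is part of routine care, so those data would exist anyway. The quality-of-life forms are most at risk.

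None of this defends the rule. A low rate of non-use makes the exclusion nearly pointless as well as nearly harmless, and a high rate makes it damaging. The retained data cannot show the size or sign of the bias.

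**Conclusion.** The concern holds, and the sentence has to be changed. As written, the plan compares self-selected users with all controls, which contradicts its own hypothesis about patients as randomised. That conclusion rests on the protocol text alone.

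The size rests on assumed values of *f* and *d*. Over f = 10% to 30% and d = 1 to 2.5, the bias is 0.1 to 0.75 points and the type I error runs from about 5% to about 25%. At f = 5% and d up to 2, it stays below 5.5%. The direction is unknown. A larger sample would not remove the bias, and replacing the excluded patients would restore numbers but not comparability.

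**What to change.** Delete the exclusion sentence and put in its place: *All randomised patients are analysed in the arm to which they were assigned, regardless of device use, and remain in all in-hospital and follow-up data collection.* Report the number of never-users and count them as zero use in the engagement outcome. If an effect among users is of interest, give it as a labelled sensitivity analysis, for example a complier-average effect with randomisation as the instrument.

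The wording costs one sentence, and data collection costs little because both arms already complete the forms. The real cost is dilution: the estimate becomes the effect of offering the device, and at 40 per arm power falls to 66.5% with 10% non-use and 56.4% with 20%. The sponsor should state an expected rate of non-use and revisit the sample size with it. On the assumptions above, 80% power needs 50 to 90 per arm for non-use of 5% to 30%.

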#### Statistical Analysis

Statistical analysis will be conducted with the SPSS Software, version 22, with an alpha of .05 set a priori for all analyses. Descriptive statistics will be used to summarize baseline demographic characteristics by study arm. Continuous variables will be compared between the two groups using a *t* test and categorical variables will be compared using a chi-square test. Pain intensity, our primary outcome, measured longitudinally, will be assessed by mixed model analysis of variance with treatment assignment as the between-group factor and time as the within-subject factor. Effect sizes will be calculated as mean group differences with standard deviations. A similar approach will be used to analyze continuous secondary outcomes while categorical outcomes will be analyzed by chi-square tests.

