##  Introduction

### Background

Lung cancer has been the most common cancer worldwide since 1985, both in terms of incidence and mortality [1-3], and it is among the top five most frequently diagnosed cancers in Italy [4]. Thoracic surgery appears to be the treatment of choice for many lung cancers. Nevertheless, depending on the type of surgery, the chest area may be painful for several weeks to months after surgery. Indeed, after a thoracotomy, patients often suffer from a persistent pain [5-7] due to the skin incision or deeper tissue injuries, costovertebral joint disruption, resection or fracture of ribs or sternum, and further irritation of the pleura by thoracostomy tubes [8,9]. This painful state has multiple implications, including respiratory failure due to limiting inspiration (because deep breathing requires stretching the incision), or an inability to clear secretions by coughing [10]. Acute pain after surgery can become chronic and persist for more than a year in 21%-67% of patients [11,12]. Moreover, a lot of clinical and demographic factors can contribute to the development of chronic postsurgical pain including psychological conditions (anxiety or depression states), previous surgery, other simultaneous pain, injuries of the chest wall, youth, female gender, and increased levels of pain and analgesic use in the perioperative period [13].

Cooley et al [14] have shown that a high level of post-operative pain in lung cancer patients may exacerbate the fear that movement or physical activity will worsen their condition. This belief can lead to catastrophic appraisals of pain sensations that promote a self-perpetuating cycle of behavioral avoidance, hypervigilance, or distress symptoms [15-18], as well as reduced social activity and global perceptions of decreased health [13]. Researchers investigating psychological aspects of persistent pain have shown that the tendency to focus on pain and to negatively evaluate one's ability to deal with pain, pain-related anxiety, fear, and helplessness are associated with increased pain, psychological distress, and physical disability [19]. Post-thoracotomy pain syndrome and its social consequences have been also investigated by a nationwide study in Denmark [20] that highlighted how partial nerve injury and general pain hyperresponsiveness influence daily activities, even 12-36 months after surgery.

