### Outcome Evaluation

#### Data Collection Materials

We will assess one primary outcome and several secondary outcomes. A number of validated instruments will be used to assess the outcomes at multiple time points during the hospitalization and follow-ups. The patients, both in the treatment and in the control arms, will be asked to complete them at specific time-points without the supervision of the research assistants. Hospital nurses will be asked if they completed all the outcome measures, as requested by the protocol, at the end of each day. Demographic and clinical information of each participant will be also collected.

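### The primary mixed model names only treatment and time; pre-specified baseline covariates would add precision at little cost, but they are not a repair of the sample-size shortfall

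*Protocol article*

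**What the plan says.** **Model.** Statistical Analysis: "Pain intensity, our primary outcome, measured longitudinally, will be assessed by mixed model analysis of variance with treatment assignment as the between-group factor". The only other term is time, taken within patients. Baseline demographics are summarised by arm. The sentence that follows, on t tests and chi-square tests between groups, can be read as applying to them. Continuous secondary outcomes, which would include anxiety on the STAI, get a similar approach.

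**Baseline data.** Data Collection Materials: "Demographic and clinical information of each participant will be also collected". The items are not listed.

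**Contact before randomisation.** Recruitment Procedure: "Once admitted in the hospital, they will be screened by a trained research assistant to verify their eligibility". Consent follows, and then random assignment, so both arms are seen before allocation.

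**Timing of measurements.** Under Primary Outcome, the first NRS falls 12 hours after surgery. By then the intervention arm has been trained and given the device. No pre-operative NRS is mentioned. The STAI is placed only at various times during the hospital stay.

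**Randomisation.** 1:1 in permuted blocks, with no stratification factor named.

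**Sample size.** The planned number, "A sample size of 80 subjects, 40 per arm", is described as "sufficient to detect a difference of 1.5 between the two groups". The spread is entered as "assuming equal standard deviation of 2.5". The error rates for the t test are given as "with 80% power, and a 2-sided alpha of .05".

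**The concern.** Permuted blocks balance the numbers in each arm, not the patients' prognosis. With 40 per arm and no stratification, some chance imbalance in prognostic factors is to be expected. A model with only treatment and time leaves that imbalance in the estimate and leaves explainable between-patient variance in the error term. Covariates measured before randomisation and fixed in advance deal with both without introducing bias.

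Part of this is urgent. Age and sex can be added to a model at any time before unblinding. A pre-operative STAI or NRS that was never scheduled cannot be recovered by a later analysis plan. The opportunity passes with each patient enrolled.

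**Working it through.** **Inputs.** From Sample Size Estimation: n = 40 per arm, difference 1.5, SD 2.5, two-sided alpha 0.05, stated power 80%. R² between baseline covariates and post-operative NRS is not in the document; it is assumed, over 0 to 0.20. Within-patient correlation is not given either; it is assumed, over 0.5 to 0.9. The number of readings is taken as 5 to 10, from a 5-day stay with ratings once or twice a day.

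**Step 1: the plan's own figure.** The noncentrality is 1.5 / (2.5 × √(2/40)) = 1.5 / 0.559 = 2.683. With 78 df the critical value is 1.991, and the noncentral t gives power 75.5% (76.5% by the normal approximation). Reaching 80% takes 45 per arm by the t test (44 by the normal approximation). The stated 80% is not reproduced; the shortfall is about 4 points.

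**Step 2: effect of covariates on that t test.** Residual SD = 2.5 × √(1 − R²); noncentral t with 77 df (one covariate).

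| Assumed R² | Residual SD | Noncentrality | Power |
|---|---|---|---|
| 0 | 2.500 | 2.683 | 75.5% |
| 0.05 | 2.437 | 2.753 | 77.6% |
| 0.10 | 2.372 | 2.828 | 79.8% |
| 0.15 | 2.305 | 2.910 | 82.0% |
| 0.20 | 2.236 | 3.000 | 84.2% |

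Power of 80% is crossed at R² of about 0.106, a multiple correlation of about 0.32 (by the normal approximation, about 0.083 and 0.29). With four covariates (74 df) each power falls by less than 0.1 percentage point, so the degrees of freedom are not a real cost.

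**Step 3: the planned analysis uses repeated readings.** If the SD of 2.5 describes one reading, and correlation is equal between all readings, the SD of a patient's mean over k readings is 2.5 × √((1 + (k − 1)ρ)/k). Power at 40 per arm without covariates:

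| Correlation ρ | k = 5 | k = 10 |
|---|---|---|
| 0.5 | 92.8% | 94.7% |
| 0.7 | 86.0% | 87.3% |
| 0.8 | 82.4% | 83.3% |
| 0.9 | 78.9% | 79.3% |

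If 2.5 is already the SD of the patient mean, nothing is gained and the table in step 2 applies. The article does not say which is meant.

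**Step 4: do the two gains overlap?** Averaging readings removes within-patient noise; baseline covariates remove between-patient variance. At k = 10 and ρ = 0.9 the variance factor is (1 + 9 × 0.9)/10 = 0.91. If covariates explain 5% or 10% of single-reading variance, it becomes 0.86 or 0.81, the SD 2.318 or 2.250, and power 81.5% or 83.7%, against 79.3% unadjusted. The gains add to each other.

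**The case against.** The strongest reply is that nothing here is wrong. An unadjusted treatment-by-time model is valid in a randomised trial, no stratification factor calls for adjustment, and a journal article may leave its covariate list to a full protocol or analysis plan that is not at hand. That stands as far as validity goes, and silence on covariates is not a decision against them. It does not fully answer the scheduling half: the article fixes the first NRS after surgery and gives no pre-operative time for the STAI, and an analysis plan cannot create those data later.

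Three stronger readings are tempting and are not supported.

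- A reader might infer that covariates would win back the missing power. That rests on an R² that the article does not supply; at 0.05 the t test stays at 77.6%. The 75.5% also belongs to a single-score t test, while the planned longitudinal model may already exceed 80% without covariates (step 3).
- A reader might infer that the trial ignores its own list of predictors. The list in the Background, which includes "youth, female gender, and increased levels of pain and analgesic use in the perioperative period", concerns chronic postsurgical pain, whereas the primary outcome is acute in-hospital pain. Perioperative pain and analgesic use, if measured after surgery, also follow randomisation and cannot serve as baseline covariates.
- A reader might take a pre-operative NRS for a true baseline of the outcome. It precedes the incision, so its predictive value for post-operative pain is unknown here.

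It is also fair to say that the article does not list age and sex by name. That they fall under demographic information is a reasonable inference, no more.

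**Conclusion.** The point holds as an improvement in efficiency. The primary model as described uses no baseline information, although some is collected and more could be had at a contact that already takes place. There is no bias and no error in the model.

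On the single-score t test the gain is about 2 points of power at R² 0.05, 4 at 0.10, 6 to 7 at 0.15 and 9 at 0.20. These figures assume the stated difference and SD, full data on 40 per arm, and an R² that the article does not support with any figure. The gain under the mixed model depends further on the within-patient correlation and on what the SD of 2.5 refers to.

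The mismatch between 40 per arm and 80% power in Sample Size Estimation is a separate matter and must be corrected there.

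**What to change.** 1. Name age and sex as fixed covariates in the primary mixed model.
2. Fix a STAI, and optionally a one-item NRS, at the screening contact before randomisation in both arms.
3. Use the baseline STAI as a covariate for pain and for the anxiety outcome; add the pre-operative NRS to the pain model if it is collected.
4. State that covariates are set in advance, are not chosen by baseline significance tests, and include no post-operative pain score or analgesic use.
5. Do not cite the adjustment as the reason why 80 patients suffice. Correct the sample-size statement separately.

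**Cost.** Age and sex should cost nothing. The rest is one short questionnaire already in the trial, at most one added pain item, and a few degrees of freedom. Patients enrolled before the change would lack the pre-operative scores, so it should be made before enrolment starts or as early as possible.
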